## Abstract

**Background/Objectives:** Complex regional pain syndrome (CRPS) is a primary pain condition that can develop in a limb after a trauma. Although the condition is rare, it may cause lifelong pain and disability. Evidence-based treatments are limited. Neurogenic inflammation induced by the release of neuropeptides, such as calcitonin gene-related peptide (CGRP), is thought to play an important role in the pathophysiology of CRPS. Recently, drugs targeting CGRP have proven to be effective and well tolerated in the treatment of migraine, but their efficacy in other pain conditions, including CRPS, is unclear. The aim of this study is to assess the efficacy of the anti-CGRP antibody fremanezumab on pain in CRPS. **Methods:** In this randomized, double-blind, placebo-controlled, proof-of-concept study, 60 adult patients with CRPS with a disease duration of 3–36 months are randomized to treatment for eight weeks with fremanezumab 225 mg or placebo administered subcutaneously at a 1:1 rate. The primary objective is to compare the change in pain intensity from baseline to the last week of treatment between fremanezumab and the placebo. Other objectives are to assess pain relief and differences in clinical signs between the groups and to examine if the effect can be predicted by CGRP biomarkers. Adverse events and blinding will also be assessed. **Conclusions:** If found effective, fremanezumab and other anti-CGRP antibodies may emerge as a mechanism-based treatment option for patients with CRPS, which could hopefully improve the overall care of patients with this devastating disease.

## 1. Introduction

Complex regional pain syndrome (CRPS) is a chronic pain condition that can occur distally in a limb following trauma or surgery. The pain is unproportionate in intensity and duration to the usual course following a similar trauma or surgery. Besides ongoing pain, the condition is characterized by sensory changes (e.g., allodynia and hyperesthesia); changes in temperature, skin color, and sweating; edema; and motor and trophic disturbances in the affected limb [1,2]. Although CRPS is an uncommon disorder, it comes with a great personal and economic burden. Indeed, among CRPS patients with a symptom duration of at least one year, pain and motor impairment are prevalent symptoms, and up to 40% of patients are unable to return to work [3]. Furthermore, psychological distress is reported more commonly among CRPS patients [4], and CRPS is associated with increased health care costs [5,6].

The etiology of CRPS is thought to be multifactorial. One of the underlying mechanisms believed to play a significant role in the pathophysiology of CRPS is neurogenic inflammation. Following the initial limb trauma, post-traumatic inflammation is seen with release of inflammatory mediators, which is thought to induce the activation of peripheral nociceptors. Besides causing pain, the activation of peptidergic nociceptors results in the release of neuropeptides such as calcitonin gene-related peptide (CGRP) and substance P [7,8]. This is believed to induce neurogenic inflammation, leading to edema, increased blood flow, and the recruitment of inflammatory cells [9,10,11]. This subsequently results in the release of cytokines, inducing further activation and sensitization of peptidergic nociceptors [12]. Thus, augmented neurogenic inflammation could explain some of the key features of CRPS, e.g., pain, swelling, heat, and redness.

Despite considerable progress in understanding the pathophysiology of CRPS, treating it is challenging. Evidence-based treatments are limited [13]. In the absence of treatment options, current treatment recommendations for pain in CRPS are the same as for neuropathic pain [14,15].

Recently, drugs targeting CGRP have become available and have been shown to be effective in the treatment of migraine [16,17]. However, the role of these anti-CGRP antibodies in other pain conditions is sparsely elucidated. A recently conducted randomized controlled trial on the efficacy of erenumab, an anti-CGRP antibody, on trigeminal neuralgia showed no effect on pain [18]. In a small retrospective study of patients with both migraine and neuropathic pain receiving treatment with anti-CGRP antibodies for their migraine, the patients reported a 41.7% reduction in their neuropathic pain [19]. While the role of CGRP in neuropathic pain is uncertain, the role of CGRP in CRPS is thought to be more crucial. Indeed, preclinical and clinical studies suggest that CGRP mediates pain and inflammation in CRPS [11,20,21,22,23,24]. This makes CGRP a possible target for a mechanism-based treatment approach to CRPS. To the authors’ knowledge, no prior studies have investigated the efficacy of anti-CGRP antibodies on pain in patients with CRPS.

The main aim of this study is to investigate the efficacy of fremanezumab, a drug targeting CGRP, on pain in patients with CRPS. The secondary aims are to assess pain relief and differences in clinical signs between the groups and to explore if the effect can be predicted by CGRP biomarkers.

## 2. Materials and Methods

### 2.1. Study Design and Settings

The study is designed as an investigator-initiated randomized, double-blind, placebo-controlled, proof-of-concept single-center study with two parallel groups. It is being conducted at the Danish Pain Research Center (DPRC), Department of Clinical Medicine and Department of Neurology, Aarhus University and Aarhus University Hospital, Denmark. The study plans to include 60 patients. Patients are randomized to one of two arms: fremanezumab 225 mg or placebo (isotonic saline) administered subcutaneously at a 1:1 rate. The study comprises a baseline period of one week and a treatment period of eight weeks (Figure 1). Outcomes are evaluated at the end of the eighth week.

### 2.2. Recruitment of Participants

The patients are recruited from the outpatient pain clinic at the Department of Neurology at Aarhus University Hospital, other pain clinics and hospital departments in Denmark, and through advertising. The written patient information is forwarded to the interested patients, and a telephone interview is conducted. During the telephone contacts, the patients are prescreened for eligibility, and information is given about the trial and what participation in the trial implies for the patients. If the patients are deemed eligible following the prescreening, they are invited to a screening visit at the DPRC, where written informed consent is obtained.

### 2.3. Study Visits

All visits are planned at the beginning of the study. Visit 2 is defined as day 1. All study visit days are calculated from this visit date (Table 1).

At visit 1 (screening visit), the patient sits down with a member of the study team, discusses any additional questions, and provides informed consent. After informed consent is obtained, the patient is further assessed for study eligibility. Previous and current medical histories are obtained, and focused neurological and physical examinations are performed to establish or confirm the CRPS diagnosis, and for fertile women, a pregnancy test is taken. The patients are trained to report pain intensity.

Registration in the pain diary starts in the baseline period. If visit 1 is scheduled for more than seven days before visit 2, the patients are instructed to fill out the pain diary for the last seven days minimum preceding visit 2. The patients should have an average daily pain (ADP) intensity of at least 4 and not above 9 on a numeric rating scale (NRS) from 0 to 10 (0 = no pain; 10 = worst possible pain) in the baseline period. This is not revealed to the patient.

At visit 2, the pain diary is used to confirm the inclusion and exclusion criteria (Table 2). Patients are, thereafter, randomized to treatment with fremanezumab or placebo. They receive the first dose of the study drug, and outcomes are accessed (see section on outcomes). Registration in the pain diary continues until the last week of treatment (week 8).

At visit 3, after four weeks of treatment, patients receive the second dose of treatment. An assessment of concomitant medication and any potential side effects is conducted, and blood pressure and pulse are measured. Additionally, a questionnaire on pain relief is filled in. Patients will not receive the second dose of study medicine if the side effects are unacceptable or if they wish to stop for other causes, but all patients who have taken at least one of the two doses of study drug or placebo are asked to continue to participate in the study as described below.

At visit 4, after the treatment period of eight weeks, outcomes are assessed again. An assessment of concomitant medication and any potential side effects and completion of the study is also conducted.

During the treatment period, the patients are contacted by telephone (at least twice and more often if necessary) and interviewed in a standardized manner to ensure compliance and to collect data on safety, side effects, and concomitant medication. Additional contact may be arranged if necessary.

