**Enrollment**:							
Informed consent	X						
Eligibility screen	X		X				
Demography	X						
Medical and medication histories	X		X		X		X
Pain report training	X						
Physical examination	X		X				X
Pulse and blood pressure	X		X		X		X
Pregnancy testing	X						
Randomization			X				
Concomitant medication use	X		X	X	X	X	X

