**Exclusion Criteria**	
1.	Other causes of pain and/or inflammation in the same area as CRPS or other concomitant pain/inflammation that cannot be distinguished from CRPS
2.	Spreading of CRPS to other extremities according to IASP criteria for spreading of CRPS
3.	Initiation of new medications within one month prior to inclusion, such as gabapentin, pregabalin and/or capsaicin (Qutenza), botulinum toxin type A, lidocaine patches (Versatis), TCAs or SNRIs, and corticosteroids prior to enrollment or for the duration of the randomized placebo-controlled phase of the study. Current and ongoing pain treatment will be allowed in stable doses (anticonvulsants, antidepressants, tramadol, paracetamol, and NSAIDs)
4.	Poor compliance or patients who cannot cooperate to report pain diary
5.	Unable to understand written and/or spoken Danish
6.	Severe depression, other significant psychiatric diseases, alcohol, or drug abuse
7.	Pregnancy or lactation
8.	Women of child-bearing potential (defined as any woman or adolescent who has begun menstruation) unless they use an acceptable effective contraception measure during the study and at least 6 months after or their male partner is vasectomized and their sole partner
9.	Known allergy to any component of fremanezumab
10.	Planned surgery
11.	Clinically significant and severe cardiovascular, cerebral, hepatic, or kidney disease

ADP: average daily pain; IASP: International Association for the Study of Pain; NRS: numeric rating scale; NSAID: nonsteroidal anti-inflammatory drug; SNRI: serotonin and norepinephrine reuptake inhibitor; TCA: tricyclic antidepressant.

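### The only scheduled pregnancy test falls 7 to 30 days before the first dose, so no test confirms the pregnancy exclusion when dosing starts

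*Protocol article*

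**What the plan says.** Section 2.3 (Study Visits) places the test among the screening procedures at visit 1: "for fertile women, a pregnancy test is taken". It mentions no test at visits 2, 3 or 4. In Table 1 the row "Pregnancy testing" carries a single mark, under visit 1.

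Table 1 puts visit 1 at day −7, with an allowed range of −7 to −30. Section 2.3 says "Visit 2 is defined as day 1", and randomisation and the first injection take place at that visit. The second injection is at visit 3, day 28 (−3/+7).

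Table 2 makes "Pregnancy or lactation" exclusion criterion 7. Criterion 8 excludes women of child-bearing potential "unless they use an acceptable effective contraception measure during the study and at least 6 months after", or unless their only partner has had a vasectomy.

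Other provisions bear on the same risk:
- Table 1 marks "Eligibility screen" at visits 1 and 2.
- Table 1 marks "Medical and medication histories" at visits 1 to 4.
- Table 1 marks a physical examination at visits 1, 2 and 4.
- Section 2.3 provides for telephone interviews during treatment "to collect data on safety, side effects, and concomitant medication".

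For the visit 2 eligibility check, the only instrument that section 2.3 names is the pain diary.

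**The concern.** Exposure to the study drug starts at visit 2, but the one objective check on criterion 7 is made a week to a month before that. A woman who is not detectably pregnant at visit 1 may be pregnant when she receives dose 1, and the schedule contains nothing that would show it. The second injection is also given without a test.

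The plan itself treats exposure in pregnancy as a real concern, since it requires contraception for at least six months after the study. A negative result up to a month old at the first injection does not match that level of care, particularly as visit 2 is already an on-site visit.

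What is at stake is participant safety and correct application of an eligibility criterion. The treatment comparison is not affected.

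**Working it through.** The check is day arithmetic on the visit windows.

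**Inputs (Table 1 and section 2.3)**
- Visit 1, pregnancy test: day −7, window −7 to −30.
- Visit 2, randomisation and dose 1: day 1.
- Visit 3, dose 2: day 28 (−3/+7), that is, day 25 to day 35.

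**Formula.** Gap = day of dose − day of test. If the calendar has no day 0 (day −1 is followed by day 1), subtract one for any interval that crosses zero. The article does not say which convention it uses, so both are shown.

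**Current schedule**

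| Interval | No day 0 | With a day 0 |
|---|---|---|
| Test to dose 1, nominal | 1 + 7 − 1 = 7 | 1 + 7 = 8 |
| Test to dose 1, longest | 1 + 30 − 1 = 30 | 1 + 30 = 31 |
| Test to dose 2, nominal | 28 + 7 − 1 = 34 | 28 + 7 = 35 |
| Test to dose 2, shortest | 25 + 7 − 1 = 31 | 25 + 7 = 32 |
| Test to dose 2, longest | 35 + 30 − 1 = 64 | 35 + 30 = 65 |

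Without a day 0, the plan's own screening window reproduces as 7 to 30 days before dose 1. The choice of convention changes each figure by one day and alters nothing in the conclusion.

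**Test moved to visit 2 (day 1)**
- Dose 1: 1 − 1 = 0 days.
- Dose 2, nominal: 28 − 1 = 27 days.
- Dose 2, range: 25 − 1 = 24 to 35 − 1 = 34 days.

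A repeat test at visit 3 would bring the second gap to 0 days as well.

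**What the other safeguards can show**
- *Eligibility screen, history and telephone interviews:* as described, these depend on what the patient knows and reports.
- *Physical examination at visit 2:* it would not reliably reveal an early pregnancy.
- *Contraception:* it prevents pregnancy but does not detect one.
- *Pain diary:* it carries no information on pregnancy.

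**The case against.** The strongest reply is that nothing in the plan is misstated. Text and table agree, fertile women are tested, pregnancy is excluded, and contraception is mandatory. Testing at screening and relying on contraception afterwards is a recognisable design.

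The proposed move also leaves dose 2 to be given 24 to 34 days after a test. If contraception is good enough for that interval, it could be argued that it is good enough for the 7 to 30 days before dose 1. A visit 2 test can also miss a very recent conception, so a gap of 0 days does not prove that the patient is not pregnant. The trial plans only 60 patients, the benefit is not quantified, and the full protocol may contain a check that the article does not show.

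Parts of this stand. Contraception remains the main safeguard between doses, no test is conclusive, and the expected number of exposed pregnancies cannot be calculated from the documents.

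The objection does not justify the present timing, though. Moving the test shortens the interval to both doses: from 7 to 0 days for dose 1, and from 34 to 27 days nominally for dose 2 (no day 0 counted). No protection from study-drug exposure is lost, because no study drug is given before visit 2.

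Nor is this an inference from silence. The article gives a full visit-by-visit schedule and places the test at one named visit. If the full protocol does test at visit 2, Table 1 needs correcting.

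**Conclusion.** The concern holds. The only scheduled pregnancy test is nominally about 7 days and at most about 30 days old at dose 1. At dose 2 it is nominally about 35 days old, with a range of about 31 to 65 days across the two day-counting conventions. Criterion 7 is therefore not confirmed by a test at either injection.

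This is a modest patient-safety weakness that the sponsor should correct because doing so is cheap. It has no bearing on the estimand, the sample size or the primary analysis. The number of women of child-bearing potential and the contraceptive failure rate are not given, so no probability of an exposed pregnancy is claimed.

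The conclusion rests on the published schedule being complete for this procedure. The recommended fix assumes a test that gives its result within the visit; the article does not state the type of test.

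**What to change.** In Table 1, move the pregnancy-testing mark from visit 1 to visit 2. In section 2.3, move the corresponding clause to the visit 2 description, and require the result to be available before randomisation and the first injection. Keep criterion 8 unchanged as the safeguard between doses. A repeat test before the visit 3 injection is an option for the sponsor; the recommendation does not depend on it.

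**Cost.** The change needs no new visit and no additional procedure. An occasional pregnancy would be found after the baseline diary week instead of at screening, which wastes that week for the patient and the site. A small amendment to a recruiting trial is needed. Section 3 gives inclusion as running from December 2023 to an expected July 2027, so participants still to be enrolled would benefit.

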### 2.4. Study Procedures

The study procedures are defined as follows:Pain diary: Patients fill in a pain diary, where they report the mean ADP and the least and worst pain in the previous 24 h. It is preferred that the patients complete the diary electronically via REDCap (Research Electronic Data Capture) hosted at Aarhus University [28,29]; otherwise, they are provided with a paper diary.Demographics: Interview questions include those regarding age, sex, race, ethnicity, education, and occupational status. Questions regarding limb domain before CRPS and CRPS duration are also asked.Blood samples: We perform a measurement of inflammatory markers in serum. A total of 10 mL blood is drawn at visits 2 and 4, and the specimen is refrigerated and stored in a biobank at Aarhus University Hospital.Skin biopsy: Biopsy is performed following published guidelines from the most painful area on the dorsal site of the affected limb and corresponding limb (3 biopsies) [30]. After intradermal injection of 1% lidocaine, a skin biopsy is obtained using sterile technique with a disposable 3 mm punch. Samples are fixed with Zamboni fixative overnight and then cryoprotected in 20% sucrose 0.1 M phosphate buffer. The biopsy specimen is refrigerated and stored in a biobank at Aarhus University Hospital. CGRP and other markers of inflammation are measured and quantified in skin biopsies using stereology [31].Quantitative sensory testing (QST): QST is a psychophysical method used to examine the function of the sensory nervous system using standardized thermal and mechanical stimuli, as proposed by the German Research Network on Neuropathic Pain. We measure the cold and warm detection thresholds (CDT and WDT), cold and heat pain thresholds (CPT and HPT), dynamic mechanical allodynia (DMA), mechanical detection and pain thresholds (MDT and MPT), and wind-up ratio (WUR), performed at the most painful area and at a corresponding non-painful area on the contralateral limb [32].Outcomes: See Section 2.7 on outcomes.

### 2.5. Randomization and Blinding

Randomization is carried out at a 1:1 rate, stratified by sex, via computer-generated randomization in REDCap using block sizes unknown to the investigators. Randomization is carried out after the baseline period if the patients meet the criteria of at least 4 on an NRS from 0 to 10.

It is not possible to make the active drug and placebo syringes identical in appearance, and they are, therefore, prepared and administered by two unblinded third-party personnel (to ensure double control) at the study site. The active substance comes in a package from the manufacturer, and the information on the package is not covered by a research label. The placebo (isotonic saline) is prepared on the study site in a separate room from where the subject receives the treatment. The needles are identical, and the subject is blindfolded during the injection. Hence, the study is double-blind (patients, health care providers, and investigators/study personnel). The sequence of the randomization numbers is only available to the unblinded personnel. The code for randomization is stored in a locked room until the study is completed. For each randomization code, there is a sealed envelope with information on the treatment given. The code envelope is only unsealed/opened if continued treatment requires knowledge of the randomization code.

### 2.6. Intervention

Fremanezumab 225 mg or placebo (isotonic saline) is given via subcutaneous injection every four weeks: in total, twice during the treatment period of eight weeks (at visits 2 and 3). The injections are administered on the study site by unblinded study personnel (see Section 2.5 on randomization and blinding).

Due to the risk of hypersensitivity reactions, the participants are monitored at the study site at least 30 min after the administration of the study drug.

### 2.7. Outcomes

Primary outcomes are as follows:1.Difference between groups (placebo vs. active treatment) in the change in self-reported daily ratings of mean ADP intensity in the affected limb from the baseline week (week −1) to the last week of treatment (week 8), as experienced during the past 24 h, rated on an 11-point NRS from 0–10 (0 = no pain; 10 = worst possible pain): the primary outcome is validated and recommended as a first Core Outcome Measurement set for complex regional PAin syndrome Clinical sTudies (COMPACT) and a standard measure of chronic pain in clinical trials [33,34,35,36].

Secondary outcomes are as follows:Difference in pain relief on a 6-point scale—complete, good, moderate, mild, none, or worse—assessed at visits 3 and 4.Difference in the change in the mean CRPS Severity Score (CSS) from the end of baseline to the end of weeks 4 and 8: CSS scores will also be divided into two sub-categories: symptoms and signs [37,38] (assessed at visits 2–4).Differences in the area and intensity of mechanical allodynia, assessed by brushing a soft brush (Somedic) twice at a speed of 1–2 cm/s: the area is measured in cm and the intensity rated on an NRS (0–10) and compared to the unaffected site (assessed at visits 2–4).The relationship between the primary outcome measure and the duration of CRPS (measured in months).

Tertiary outcomes are as follows:Differences between groups in the Patient Global Impression of Change (PGIC), assessed at visit 4: PGIC measures the patients’ overall change from baseline on a 7-point scale [39].Number of patients with a reduction of ≥30% and ≥50% reduction in the mean ADP in week 4 and week 8 compared to the baseline.Mean values of ADP for all 8 weeks.Differences between groups in the change in the least and worst pain in the previous 24 h, rated on an NRS from 0 to 10, assessed during the baseline week (−1) and the last week of treatment (week 8).Correlations between baseline measures of CGRP nerve fiber density in skin (mm^2^) and immune cells, i.e., Langerhans cells, macrophages, and keratinocytes, inflammatory markers in serum, skin flare response (FR) (measured as a % change in blood flow from baseline over time) [40,41], and treatment outcomes as measured by the mean ADP and CSS (visits 2 and 4).To measure differences from the baseline (visit 2) to visit 4 in inflammatory markers in serum, CGRP nerve fiber length density in skin (mm^2^), and immune cells, i.e., Langerhans cells, macrophages, and keratinocytes and skin FR.To measure differences in passive coping and pain catastrophizing at baseline (visit 2) and at visit 4, assessed using the Pain Self-Efficacy Questionnaire (PSEQ) and Pain Catastrophizing Scale (PCS) [42,43,44].Differences in symptoms of depression and anxiety, pain interference, fatigue, and sleep disturbance, assessed using the Patient-Reported Outcome Measurement Information System (PROMIS-29) short form [45,46,47,48,49,50,51] (visits 2 and 4).Differences in the area and intensity of evoked pain assessed via bedside sensory testing: the pain intensity is measured at the site of maximal pain or as close as possible; cold allodynia is assessed twice using a 20 °C cold Somedic thermal roller, and the same procedure is undertaken for warm allodynia (40 °C); pinprick hyperalgesia is assessed using a pinprick stimulator as the difference in the pain score of 2 stimulations at a control site and the pain site; pain is rated on an NRS (0–10); hyperpathia is assessed via repetitive mechanical pinprick stimulation at a rate of 2 HZ for 60 s, and the pain is rated using an NRS (0–10) at 10 s intervals until the pain ceases [52] (visits 2 and 4).Differences in z-scores and percentages of patients with abnormal scores on the QST, in a reduced version of the protocol by the German Network for Studying Neuropathic Pain [32] (visits 2 and 4): we will measure the CDT, WDT, CPT, HPT, DMA, MDT, MPT, and WUR at the most painful area and at a corresponding non-painful area on the contralateral limb.Differences in extremity edema of the affected and unaffected limb using the gold standard water displacement method based on Archimedes’ principle [53,54] and the circumference measured in cm (visits 2 and 4).Differences in skin temperature of the affected and unaffected limbs using infrared thermometer [55] (visits 2 and 4).Differences in the measurement of Timed Up and Go (TUG) for lower extremities and the Nine-Hole Peg Test (9HPT) for upper extremities (measured in seconds) (visits 2 and 4).The difference in the intensity of the various pain symptoms assessed using the Neuropathic Pain Symptom Inventory (NPSI) [56] (visits 2 and 4).Percentages of patients with adverse effects registered in the treatment period, assessed via open-ended questions in both treatment groups.Differences in pain sensitivity at baseline (visit 2) and visit 4, assessed by using the Pain Sensitivity Questionnaire (PSQ) [57].

Other outcomes are as follows:Assessment of blinding: At the end of the blinded phase (visit 4), the assessment from the patient and investigator is recorded in the case report form (CRF) (whether they think the patient received an active treatment or placebo or do not know, as well as what reason this is based on (side effect, effect, or something else)).Assessment of patients’ expectation to the study drug (visit 2).A qualitative assessment of any difference in outcomes based on the pain intensity ratings in the pain diary and pain relief scores (visit 4).

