### 2.9. Sample Size Calculation

According to a previous double-blind, placebo-controlled study on intramuscular neridronate in patients with CRPS type 1, we expect an average reduction in pain intensity in patients with CRPS of 4 on an NRS (0–10) and a placebo response of 2 on the same scale. With a similar standard deviation in both groups (placebo and patients) of 2.5, a type 1 error rate of 5%, and a power of 80%, a sample size of 26 patients in each group yields a minimum detectable effect of 2 (0–10 NRS) [58]. As there are no comparable studies in CRPS, we aim for 26 patients in each group (30 to account for dropouts), as stated in the power calculation above. We will also accept 20 patients (with a power 70) and 23 patients (with a power 75) in each group, although with less power (calculation based on the same study).

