### 2.10. Statistics

Baseline characteristics, including demographics and disease characteristics, will be described using means with the standard deviation (SD) or medians with the interquartile range (IQR) for continuous variables and numbers with percentages for categorial variables. We will use a flow chart to describe the inclusion of patients, including dropouts, loss to follow up, and missing data. We will also report the number of screen failures.

Statistical analysis of the primary outcome will be performed using a *t*-test (parametric) or Mann–Whitney U-test (non-parametric), where applicable. Non-dichotomous primary and secondary outcomes will be performed using a *t*-test or Mann–Whitney *U* test, where applicable. For the primary outcome, the delta values from the average pain intensity in the baseline week to the last treatment week (last 7 days) will be used. Response rates and other dichotomous data are analyzed using Fisher’s exact test or χ^2^ test. Spearman’s correlations coefficient will be used to assess predictors.

The analysis for the primary outcome is the intention-to-treat (ITT) population. The last observation carried forward (LOCF) will be the primary imputation method, and the baseline observation carried forward (BOCF) will be used as a secondary imputation method for those that do not finish the pain diary. Missing data will not be replaced. All patients who have received at least one injection will be encouraged to stay in the study, complete the diary, and come for the remaining visit after 4/8 weeks.

Significance is considered at the 5% level. If there are changes to the original statistical plan, the type of change and the date of the change will be documented, and the document will be signed by the sponsor.

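### The planned week 8 tests of CSS and mechanical allodynia leave out patients seen at visit 3 but not visit 4, which biases the comparison if that loss depends on the week 4 result and differs between arms

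*Protocol article*

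**What the plan says.** **Outcomes.** Section 2.7 of the protocol article lists among the secondary outcomes the "Difference in the change in the mean CRPS Severity Score (CSS) from the end of baseline to the end of weeks 4 and 8", with symptom and sign sub-scores. It also lists the area and intensity of mechanical allodynia, "the intensity rated on an NRS (0–10) and compared to the unaffected site (assessed at visits 2–4"). Table 1 marks CSS and bedside sensory testing at visits 2, 3 and 4.

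**Test.** Section 2.10 states: "Non-dichotomous primary and secondary outcomes will be performed using a *t*-test or Mann–Whitney *U* test, where applicable".

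**Population and missing data.** Section 2.10 continues: "The analysis for the primary outcome is the intention-to-treat (ITT) population". It names LOCF as the primary imputation method and BOCF as the secondary one "for those that do not finish the pain diary. Missing data will not be replaced".

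**Expected loss.** Section 2.9 says "we aim for 26 patients in each group (30 to account for dropouts").

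**Retention.** Under section 2.3, patients who have had at least one dose "are asked to continue to participate in the study as described below". Section 2.10 repeats that they are encouraged to complete the diary and to attend the remaining visit.

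**The concern.** CSS and allodynia are examined in the clinic and are not diary items. A week 8 change therefore needs a visit 4 examination, and the imputation rules, read as diary rules, do not supply one. The week 8 test becomes an analysis of visit 4 attenders.

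Differences in clinical signs between the groups are a stated secondary aim (section 1), and these two outcomes carry it. If placebo patients who are doing badly at week 4 leave more often, the placebo patients still present at week 8 look better than the randomised group, and a real effect is understated. If patients without benefit leave mainly from the active arm, the effect is overstated. In both cases the week 4 score, already collected, holds information about the missing week 8 score that the planned test does not use.

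**Working it through.** **Step 1: the plan's own figure.** Inputs from section 2.9 are a difference of 2, an SD of 2.5, a type 1 error of 5% (taken as two-sided, since sidedness is not stated) and 80% power. The standardised effect is 2/2.5 = 0.8. The noncentral t calculation gives 25.5, so 26 per arm, with 80.7% power. Power is 75.6% at 23 per arm and 69.3% at 20. The stated figures reproduce.

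**Step 2: the loss the plan allows for.** (30 − 26)/30 = 4/30 = 13.3% per arm. This is an allowance for all dropout, and section 2.9 does not say when it occurs.

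**Step 3: what drives the bias.** Let x be the week 4 change and y the week 8 change, in SD units, with correlation ρ. If loss after visit 3 depends only on x, the mean of y among attenders in an arm is shifted by

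 ρ × (mean x of attenders − mean x of all patients in that arm).

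The bias of the week 8 difference is the gap between the two arms' shifts. It is zero when both shifts are zero (random loss) or equal (the same rate and the same dependence on x in both arms).

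**Step 4: a bound for loss in placebo only.** Suppose placebo loses exactly its worst 13.3% at week 4 and the active arm loses at random. The cut-off is z = 1.11, the normal density there is 0.215, and the shift in mean x is 0.215/0.867 = 0.248. The bias is 0.5 × 0.248 = 0.12 SD to 0.8 × 0.248 = 0.20 SD. A very large simulation (1,000,000 patients per arm) gives the same 0.12 to 0.20.

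**Step 5: a softer pattern at trial size.** The settings are 30 per arm, four lost per arm, true difference 0.8 SD at week 8 (borrowed from the pain outcome) and 0.5 SD at week 4. Late placebo losses are drawn with weight exp(1.5 × week 4 score); all other losses are random. None of these settings except the 4 of 30 and the ratio 2/2.5 comes from the documents.

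| Losses per arm after visit 3 | Estimate on visit 4 attenders, ρ = 0.5 / 0.7 / 0.8 | Shortfall from 0.80 |
|---|---|---|
| 1 of 4 | 0.77 / 0.76 / 0.76 | about 3–5% |
| 2 of 4 | 0.755 / 0.736 / 0.726 | about 6–10% |
| 4 of 4 | 0.714 / 0.688 / 0.672 | about 11–17% |

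The shortfalls are rounded to cover repeated runs. In the last row, power of the t-test is about 69–72%.

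**Step 6: the same data with the week 4 value used.** Within each arm, the estimate is mean y of attenders + b × (mean x of all seen at visit 3 − mean x of attenders), where b is the slope of y on x. This recovers about 0.80 SD in every row. With all four losses late, power is about 81–85%.

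**Step 7: loss that is random or alike in both arms.** Both methods average about 0.80 SD, and their power differs by about −1 to +3 percentage points.

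**The case against.** - **A reader might infer that the week 8 comparison is biased as planned.** The documents do not support this. Bias needs loss that depends on the week 4 result and also differs between arms, and nothing in the article shows such a pattern.
- **A reader might infer that the visit 3 value is thrown away.** It is not. The change to week 4 is an outcome in its own right, and later loss does not touch that comparison. The value is unused only in the week 8 test.
- **The size rests on assumptions.** The article gives no SD, correlation, or timing of loss for these outcomes. The standard error at 26 per arm is √(2/26) = 0.28 SD, so even the shortfall with all four losses late (0.09 to 0.13 SD) is under half a standard error. This stands.
- **The plan tries to keep patients.** Stopping treatment is not the same as missing visit 4, and one visit remains after the second dose. This limits the loss but does not say how the remainder is analysed.
- **LOCF might be meant generally.** The diary clause follows the mention of BOCF, so LOCF could be read as covering CSS and allodynia too. That reading is possible, but it conflicts with the next sentence, which rules out replacing missing data. LOCF for the diary and nothing elsewhere is the reading that makes the two sentences agree.
- **This could be left to an analysis plan.** Silence could be. But section 2.10 states the test and a no-replacement rule, so the point concerns what is fixed.
- **A normal model is not clearly better for allodynia area.** If the area is skewed or has many zeros, the planned rank test is defensible. This stands and limits the fix.

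**Conclusion.** The point holds in conditional form. On the most natural reading of section 2.10, a patient seen at visit 3 but not at visit 4 leaves the week 8 tests of CSS and allodynia, although a related measurement is in hand.

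If that loss depends on the week 4 result in the placebo arm only, with the assumed 0.8 SD effect and correlation of 0.5 to 0.8, the week 8 difference is about 6–10% too small with two late losses per arm and about 11–17% too small with four. Selective loss of non-responders in the active arm would act in the opposite direction. With random loss, or loss alike in both arms, there is no bias and only a slight loss of precision.

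Confidence in the reading of the text is fair; confidence in the size is low. The primary outcome comes from the diary and is not affected. The change is worth making because it costs little, not because a bias has been shown.

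**What to change.** In section 2.10:

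1. Analyse change in CSS (total, symptoms, signs) and in allodynia intensity with one repeated-measures model over visits 3 and 4. Include arm, visit, arm-by-visit, the visit 2 value and sex (the stratification factor), with an unstructured covariance. Include all randomised patients with at least one post-baseline value, and report the week 4 and week 8 differences from this model.
2. Keep the two-sample test as a sensitivity analysis.
3. For allodynia area, keep a rank-based analysis if the data are skewed or zero-inflated.
4. State that LOCF and BOCF apply to the pain diary only.

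**Cost.** A wording change and a little more analysis, with no new data, visits or patients. Section 2.10 already provides for dated and signed changes to the statistical plan, and section 3 expects inclusion to run until July 2027.

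**Downside.** The model assumes that loss is explained by the observed baseline and week 4 values. It does not recover patients lost before visit 3.
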